##### Unexpected adverse effects

Any unexpected adverse effects of participating in the trial will be recorded.

##### Acceptability of the intervention

Responses to a feedback questionnaire asking participants about their experience of the intervention will be recorded. The feedback questionnaire includes questions with rating scales and questions with written responses.

#### Secondary objective—collect data on clinical measures

Questionnaire measures of depression, anxiety and self-esteem as well as questionnaires and tasks that measure the proposed mechanisms of therapeutic change will be included. All measures are administered at each of the three assessment time points, except the ‘daily mood ratings and social connectedness’ and the ‘memory recall task’ which are only administered at pre-intervention and post-intervention time points.Mood and Feelings Questionnaire (MFQ). The MFQ [59] is a self-report measure of depression. The long version of the MFQ (33 items rated on a 3-point Likert scale from 0 to 2) will be used at each of the three assessment time points and is the primary clinical measure for this trial. Scores range from 0 to 66 with higher score indicating more symptoms of depression. The MFQ has been used extensively in research and community settings; it is recommended by the National Institute of Clinical Excellence [57] and is routinely used in Child and Adolescent Mental Health services in the UK. The MFQ has been shown to be reliable and valid with scores of over 29 indicating a likely current major depressive episode and scores of over 20 indicating the presence of ‘any mood disorder’ [46]. For the screening stage, the four risk items will be removed from the MFQ due to ethical considerations in mass testing conditions. The MFQ at the screening stage will therefore consist of 29 items and a clinical cut-off score of 17 will be used at screening to reflect this. The shorter version (12 items) will also be administered at the beginning of each intervention session alongside a risk item to monitor any change in risk. The shorter version is preferred for intervention sessions given its quicker completion time.Screen for Child Anxiety Related Disorders (SCARED). The SCARED [60] is a self-report measure of anxiety. The SCARED consists of 41 items, rated on a 3-point Likert scale from 0 to 2. Total scores on the measure range from 0 to 82 with higher scores indicating more anxiety. The SCARED also has five subscales: panic disorder or significant somatic symptoms, generalised anxiety disorder, separation anxiety, social anxiety disorder and significant school avoidance. The SCARED shows excellent internal consistency, test re-test reliability, and concurrent and discriminate validity [60, 61].Revised Impact of Event Scale: child version (RIES-C). The 13-item self-report version of the RIES-C [62] will be administered to measure post-traumatic stress symptoms in reference to a negative event. Items are rated on a 4-point Likert scale (measured 0, 1, 3, 5) with higher scores indicating more symptoms of post-traumatic stress. There are also three subscales on the RIES-C: intrusion, avoidance and arousal. The RIES-C has been established as a good screen for PTSD diagnosis [62] with good internal reliability (Cronbach’s *α* = .80 [63]). The RIES-C also includes a single-item measure of intrusive image frequency.Children’s Response Style Questionnaire (C-RSQ). The C-RSQ [64] measures cognitive responses to low mood using 25 items. It is a self-report measure with three subscales: ruminative responses, distractive responses and problem-solving responses. Young people are asked to rate how frequently they use certain responses to low mood. Items are rated on a 4-point Likert scale (measured 1 to 4) with higher scores indicating a greater tendency to engage in that response style. Previous studies have demonstrated good validity and good internal consistency [64, 65].Rosenberg Self Esteem Scale (RSES). The RSES [66] is a ten-item self-report measure of self-worth. Scores range from 1 to 4 with higher scores indicating greater self-esteem. The RSES is widely used across the age range, and previous studies have demonstrated reliability, validity and good internal consistency in an adolescent sample [67–69].Self-Concept Clarity scale (SCCS). The SCCS [70] measures a person’s confidence in being able to define themselves clearly. It is a self-report measure consisting of 12 items rated on a 5-point Likert scale (scored 1 to 5), with higher scores indicating greater self-concept clarity. Previous studies have demonstrated the validity and reliability of the SCCS [70], and it has been used in an adolescent population [71].The Prospective Imagery Task (PIT). The adult version of the PIT [13, 17] has been adapted for use in young people. Participants are asked to read 14 scenarios, which includes 7 negative and 7 positive scenarios (e.g. ‘You will make good and lasting friendships’). Participants are asked to imagine each happening to them and then rate the vividness of the generated mental image on a 5-point scale (from 1 to 5). In addition to the adult version, participants will also be asked to specify how often they have had this image before on a 5-point scale (from 1 to 5). Higher scores indicate more vivid or frequent images of the future on the two scales.Autobiographical Memory Task (AMT). The AMT [72] will be administered to measure memory specificity, following Williams and Broadbent procedure and coding scheme. Participants are asked to give a specific memory to ten cue words (five positive; five negative), presented in a randomised order orally and in writing (printed on index cards). Participants are given 60 s to respond to each cue word. Before beginning, participants are given the opportunity to practise two cue words (*beach* and *egg*) and are given feedback on their responses. Each memory will be coded as (1) ‘specific’ if the memory was of an event occurring at a particular place and time and lasting less than a day, (2) ‘general categorical’ if the memory was of a repeated event, (3) ‘general extended’ if the memory referred to an event that lasted longer than a day, (4) ‘semantic associate’ if the response was not a true autobiographical memory, or (5) ‘no response’. The AMT will be audio-recorded and the responses co-rated.Daily mood ratings and social connectedness. Participants will be asked to rate ‘How *[emotion]* they feel’ on a Likert scale from 1 (not at all) to 9 (extremely) and to specify who they are with (family, friends, on my own, other: please specify). Mood ratings will be taken to eight emotions (happy, joyful, excited, energetic, sad, angry, nervous, and upset). Participants will be asked to install an app on their mobile phone and will be prompted to complete the questions once per day for 7 days pre-intervention and 7 days post-intervention. This app prompts them to answer the survey at the same time each day and also sends a reminder for them to complete it if they have not responded within an hour. If the app does not work for certain participants’ phones, then alternative methods will be used that best suit the participant (for example, text messages).Memory recall task. A bespoke experimental task will measure participants’ emotional response to one positive autobiographical memory pre-intervention and a different positive autobiographical memory post-intervention. Participants will be asked to generate two positive autobiographical memories before attending the first assessment session and prior to randomisation. Emotional response will be measured using subjective ratings of mood (on the eight scales detailed above) as well as using a more objective psychophysiological measure, heart rate variability (HRV, recorded with Polar RCS800CX). This recall task was based on a recent experimental task using processing mode to alter positive emotional response [73].

#### Intervention development and development of training materials

Throughout the trial, qualitative descriptions of the treatment targets (e.g. negative images rescripted; positive future images generated) will be recorded. This will allow refinement of the intervention manual following trial completion and further development of training materials for teaching practitioners how to deliver the intervention.

#### Qualitative interviews

A small subset of trial participants will also be invited to take part in qualitative interviews following completion of their participation in the trial. These interviews will be conducted, analysed and reported separately from the main trial.

### Analysis plan

Primary feasibility data will be presented descriptively as outlined in the outcome measures section. Descriptive statistics will be reported for all other relevant outcomes at each time point by trial arm. This will include means (standard deviations) and medians (interquartile range) for normally and non-normally distributed variables, respectively. Frequencies and percentages will be used to summarise categorical data.

Additionally, for the secondary clinical and mechanistic outcomes, we will present between-group mean differences at the two follow-up time points in the form of standardised effect sizes with 95% confidence intervals, using both the intention-to-treat population (all participants randomised regardless of adherence to treatment) and the per protocol population (only participants adhering to treatment; defined as completing at least three sessions).

Flow through the trial will also be presented in a standard CONSORT diagram, including number approached to participate, number eligible/ineligible, number randomised, drop-outs before the end of treatment and numbers retained in the trial at 3-month follow-up.

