#### Sample size

A power calculation to determine the sample size is not appropriate for a feasibility trial, as the purpose of the trial is not to establish efficacy at this stage. However, the data from this trial could be used to provide initial estimates of the likely range of effect sizes for the intervention. The target recruitment for this feasibility trial will be *N* = 56 (28 in each arm). This was determined with reference to good practice recommendations for feasibility studies, which recommend sample sizes of between 24 and 50 [49–51]. The sample size of 50 was inflated to allow for drop-out following randomisation, which was estimated to be 10% based on similar studies [47] identifying a final sample size of 56.

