#### Recruitment, randomisation and blinding

All participants will be recruited from secondary schools and sixth form colleges in the UK. For the screening stage, information sheets will be provided and young people asked to complete the Mood and Feelings Questionnaire (MFQ, at screening the four risk items will be removed from the MFQ due to ethical considerations). Eligible participants will be contacted and provided with the information sheet for the intervention stage. Young people will be given at least 24 h to read over the information and consider taking part, as well as discuss their participation with anyone they may wish to (e.g. parent). The first assessment will then be completed at the young person’s school, which will include administering the MFQ again (33-item version) and confirming the other eligibility criteria. Once the young person has given informed consent, the full pre-intervention assessment will be administered. Whilst parental consent will not be sought, since all participants will be over age 16, we will follow each school’s recommendations for contacting parents and discussing participation. Examples of this might be contacting the parents by phone, email or letter and providing information about the trial and the opportunity to contact the team and discuss the study. A number of strategies attempting to enhance recruitment and retention have been incorporated; these include recommendations from service user consultants to deliver the intervention in schools, to ask young people about the best way to contact them to discuss the project and to not complete formal diagnostic assessments. Furthermore, specific strategies will be discussed with individual schools as to how best to recruit young people and retain them in the trial.

Following the assessment, participants will be randomly allocated to one of two interventions by the King’s Clinical Trials Unit (KCTU). Participants will be randomised in a 1:1 ratio using block randomisation via a web-based system. The sample will be stratified by school. Randomly varying block sizes will reduce the predictability of the sequence and ensure allocation concealment. The control intervention is a recommended Tier 2 intervention, which helps to address potential ethical issues related to randomisation. The randomisation system will be accessed by the chief investigator (VP) via the web interface in the time period between the pre-intervention assessment and first intervention session.

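### The secondary effect sizes are stated as between-group differences at each follow-up with no baseline or school term; as written the intervals are valid but less precise than the data allow (low severity)

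*Protocol article*

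**What the plan says.** For the secondary clinical and mechanistic outcomes, the Analysis plan section of the protocol article states: "we will present between-group mean differences at the two follow-up time points in the form of standardised effect sizes with 95% confidence intervals". It gives the time points, the scale, the interval and two analysis populations. It names no model, no covariate and no standardising SD, and it does not say whether the differences are adjusted.

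Three other statements bear on this:

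- **Baseline.** Study design and timeline places the pre-intervention assessment before randomisation. The section on the secondary objective says "All measures are administered at each of the three assessment time points". The same sentence then makes an exception for the daily mood ratings and the memory recall task, which are collected only before and after the intervention.
- **Stratification.** Recruitment, randomisation and blinding says "The sample will be stratified by school", with blocks and 1:1 allocation.
- **Use of the results.** Sample size says "A power calculation to determine the sample size is not appropriate for a feasibility trial", but adds that "the data from this trial could be used to provide initial estimates of the likely range of effect sizes for the intervention".

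**The concern.** The trial collects a pre-intervention value of each outcome and stratifies allocation by school, but the stated estimator uses neither. An analyst who follows the sentence literally would compare follow-up means only. Two things follow.

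- **Precision.** Where baseline predicts follow-up, a difference adjusted for baseline has a smaller standard error than a difference in follow-up means.
- **Chance imbalance.** With about 25 per arm, the arms can differ noticeably at baseline by chance. Part of that difference, in proportion to the correlation, passes into an unadjusted effect size.

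The article offers these effect sizes as a first indication of the likely range for a later trial, so an estimate that is avoidably noisy or shifted makes that indication less useful. If adjustment is left open, it could also be decided after an imbalance has been seen.

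**Working it through.** **Inputs from the article.** Target 56 participants, 28 per arm; 50 inflated for 10% drop-out (Sample size). 95% intervals (Analysis plan). Retention thresholds of 80% post-intervention and 70% at 3 months (Criteria for proceeding to a future trial). Entry requires an MFQ score above 20 (Inclusion criteria).

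**Inputs assumed.** The baseline-to-follow-up correlation r, the between-school intraclass correlation (ICC) and the number of schools are not given. I take r from 0 to 0.7, ICC from 0.01 to 0.10, and 5 to 10 schools. The MFQ entry cut narrows the baseline range and may lower r for that measure.

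**Step 1: the plan's own figure.** 50 / 0.9 = 55.6, rounded up to 56. This reproduces. 56 × 0.9 = 50.4, so about 25 completers per arm.

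**Step 2: unadjusted half-width** (true effect near zero, SD units, n per arm):

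t(0.975, 2n − 2) × √(2/n). With n = 25: 2.011 × 0.283 = 0.57 SD.

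**Step 3: half-width adjusted for baseline:**

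t(0.975, 2n − 3) × √(2/n) × √(1 − r²) × √(1 + 1/(2n − 4)). The last factor is the small-sample cost of estimating the slope.

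| r | Half-width, n = 25 | Ratio to unadjusted | 1/(1 − r²) |
|---|---|---|---|
| 0 | 0.575 | 1.01 | 1.00 |
| 0.2 | 0.56 | 0.99 | 1.04 |
| 0.3 | 0.55 | 0.965 | 1.10 |
| 0.5 | 0.50 | 0.88 | 1.33 |
| 0.7 | 0.41 | 0.72 | 1.96 |

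The last column is the approximate factor by which the sample would have to grow to gain the same precision without adjustment.

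At the progression thresholds the pattern is the same:

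| Retention | n per arm | Unadjusted | r = 0.3 | r = 0.5 | r = 0.7 |
|---|---|---|---|---|---|
| 80% | 22.4 | 0.60 | 0.58 | 0.53 | 0.44 |
| 70% | 19.6 | 0.65 | 0.63 | 0.57 | 0.47 |

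**Step 4: chance imbalance.** With 25 per arm the baseline difference has SD √(2/25) = 0.28 SD units. The chance that it exceeds 0.3 SD in either direction is 2 × [1 − Φ(0.3/0.283)] = 0.29. The part carried into the raw follow-up difference is r × imbalance: 0.3 × 0.3 = 0.09, 0.5 × 0.3 = 0.15 and 0.7 × 0.3 = 0.21 SD.

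**Step 5: school.** The width ratio is approximately √(1 − ICC) × t(0.975, 2n − 1 − S) / t(0.975, 2n − 2), with S schools. For n = 25 and S from 5 to 10, it is 0.997 to 1.001 at ICC 0.01, 0.977 to 0.981 at ICC 0.05, and 0.951 to 0.954 at ICC 0.10. The gain is therefore about 0 to 5%.

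**The case against.** The strongest reply is that the sentence does not say unadjusted. A baseline-adjusted difference is still a between-group mean difference, and the article condenses a fuller protocol that is not shown and may name the covariates. That stands as far as intent goes: a reader might infer that the trial team decided to leave baseline and school out, and the text does not support this. What remains is that the article fixes the estimator in some detail, and a plain reading of it yields a follow-up-only difference.

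Several stronger inferences also fail:

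- **Bias or invalid intervals.** In a randomised trial chance imbalance is not bias, and an unadjusted interval has its nominal meaning. The loss is efficiency only.
- **The intention-to-treat label is contradicted.** The Analysis plan speaks of "using both the intention-to-treat population (all participants randomised regardless of adherence to treatment", and a reader might infer that people without a follow-up score are silently dropped. The article does not say how missing outcomes are handled. It defines the set by contrast with adherence, and it states under Recruitment, randomisation and blinding that those who stop the intervention are still invited to assessments. The 70% figure is a progression threshold; the planning assumption is 10% loss.
- **School matters as much as baseline.** It does not: the gain is small, and stratification already tends to balance the arms by school.
- **Every baseline value precedes randomisation.** This is not certain for the daily mood ratings. They run for seven days before the intervention, while allocation takes place between the assessment and the first session.

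It is also fair to say that the gain depends on an unstated correlation: 3.5% in width at 0.3, and about 1% at 0.2.

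**Conclusion.** The point holds as a low-severity improvement. Taken as written, the secondary effect sizes have valid intervals that are less precise than the collected data allow. At 25 per arm, baseline adjustment would reduce the half-width from 0.57 SD to 0.55, 0.50 or 0.41 SD at assumed correlations of 0.3, 0.5 or 0.7, and would cost about 1% in width if the correlation were zero. A 0.3 SD baseline imbalance, which chance alone would exceed in about 29% of such trials, would move the raw estimate by 0.09 to 0.21 SD over the same correlations.

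Nothing in the primary objective depends on this. The feasibility data are descriptive, the sample size uses no effect size, and the stated progression criteria are recruitment time, retention and acceptability, with review of serious adverse events.

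**What to change.** Add to the Analysis plan that:

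- each follow-up difference is estimated from a model containing arm, that measure's pre-intervention score, and school as the stratification term, with small schools pooled or school entered as a random effect;
- the adjusted difference is standardised by a named SD, such as the pooled baseline SD. For the MFQ, the entry cut narrows the baseline spread, so the choice affects the scale and should be stated in advance;
- raw means and SDs by arm and time point stay as descriptives.

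For measures taken at all three time points, a mixed model is a reasonable option, because it also uses the partial data of participants lost at 3 months. Daily mood and memory recall have only pre and post values, so they need a simple baseline-adjusted model. For daily mood, say whether the ratings used as baseline precede allocation.

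The cost is a few sentences and slightly more analysis. No new data are needed, and the design, sample size and progression criteria do not change.

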#### Criteria for proceeding to a future trial

The decision of whether or not to proceed to a future definitive trial will be based on the feasibility and acceptability data. Primarily, to proceed, it will be important that recruitment for the current feasibility trial is achievable within a reasonable amount of time (2 years for full recruitment), retention rates are at least 80% at post-intervention and 70% at 3-months and an average acceptability of the ICBI intervention is rated as satisfactory or above. Not reaching these criteria does not necessarily indicate unfeasibility of a future definitive trial but may underline changes needed to the trial protocol, which will also be informed by qualitative findings regarding reasons for participation and any experiences of intervention which may impact upon retention or acceptability of the ICBI intervention. This would also be reviewed by the trial steering committee (TSC). Furthermore, any serious adverse events, serious adverse reactions or suspected unexpected serious adverse reactions that arise will be carefully reviewed by the TSC, and their advice will be followed on whether these would preclude proceeding to a definitive trial.

### Monitoring

#### Trial steering committee

A TSC has been formed. The TSC’s role is to provide oversight of trial progress and conduct (including adherence to protocol) and provide guidance for appropriate aspects of the trial. This includes monitoring and supervising the progress of the trial towards its interim and overall objectives and monitoring the rights, safety and well-being of the participants. Given the scope and nature of the trial, a data monitoring committee was not deemed necessary.

#### Criteria for discounting or modifying intervention for a given participant

The interventions will be discontinued for a given trial participant if adverse events are reported that are deemed to be associated with the intervention by the chief investigator (CI), supervisors and/or independent chair. The content of both the interventions will be tailored to the individual needs of the individual, whilst remaining consistent with the manuals.

#### Adverse events

Serious adverse events (SAE: events not necessarily caused by or related to the intervention), serious adverse reactions (SAR: events related to any duration of intervention administered to that person) and suspected unexpected serious adverse reaction (SUSAR: an adverse reaction where nature and severity of which is not consistent with the information known about the intervention in question in the view of the investigator) are defined as events that result in death, are life-threatening, require hospitalisation or prolongation of existing hospitalisation, result in persistent or significant disability or incapacity, or consist of a congenital anomaly or birth defect. All SARs and SUSARs will be reported immediately by the CI to the ethics committee within 15 days of the CI becoming aware of the event.

Adverse events (AE) (any untoward medical occurrence in a subject to whom an intervention has been administered including occurrences, which are not necessarily caused by or related to that therapy) will be monitored and recorded from randomisation to the final follow-up (3-month follow-up). As the trial will be conducted within a school setting with participants who are reporting symptoms of depression, possible AE that are likely in this population and will not be reported to the TSC are low-risk acts of self-harm (not requiring medical attention), e.g. *minor* scratching. Possible AE and serious adverse events (SAE) that are less likely but may still occur include high-risk acts of self-harm (requiring medical attention, but not medical hospital admission) and death by suicide. These will be reported to the independent chair of the TSC. Any adverse events that are considered by the CI, in consultation with the independent chair of the TSC, to be related to trial procedures in any way, or are unexpected, will be reported in timely fashion as stipulated above. These AE and SAE will be recorded and reported in full in the trial report and journal paper. In addition, risk and health service use will be assessed at each assessment time point, and a risk-monitoring question will be completed at each intervention session. The participant information sheet also contains information about who to contact if the participant feels that the study has harmed them in any way or if they wish to make a complaint about the conduct of the study.

